## Abstract

Non‐vitamin K antagonists oral anticoagulants (NOACs) have recently challenged vitamin‐K antagonists (VKAs) for stroke and systemic embolism prophylaxis in patients with non‐valvular atrial fibrillation (NVAF). Nevertheless, little information is available in routine clinical practice for France. The aim of this study is to describe the effectiveness and safety of apixaban, rivaroxaban, dabigatran or VKAs in routine clinical practice in adult NVAF patients for the prevention of stroke and systemic embolism in France. The NAXOS study is a nationwide observational retrospective cohort generated from the French national healthcare insurance database (SNIIRAM—a comprehensive in‐ and outpatient healthcare consumption database), consisting of eight distinct sub‐cohorts of anticoagulant‐naive or anticoagulant‐experienced patients diagnosed with NVAF, newly initiated with either NOACs (dabigatran, rivaroxaban or apixaban) or VKAs. Patients will be included if initiating a new anticoagulant treatment for AF during the study period from 1 January 2014 to 31 December 2016. Primary effectiveness outcome will be the incidence of stroke or systemic thromboembolic events; primary safety outcome will be the incidence of major bleeding during the exposure period. The NAXOS study will provide routine clinical practice data on the effectiveness and safety profiles of apixaban vs other NOACs and VKAs in the prevention of stroke and systemic embolism in adult patients with NVAF in clinical practice conditions in France.

AbbreviationsAFatrial fibrillationCMAContinuous Measure of Medication AcquisitionCNILFrench data protection commission, “*Commission Nationale Informatique et Libertés*”ICDInternational Classification of DiseasesIDSInstitute of health data, “*Institut des Données de Santé*”LTDlong‐term disease, “*Affection Longue Durée*”NOACsnon‐vitamin K antagonist oral anticoagulantsNVAFnon‐valvular atrial fibrillationPMSIFrench Hospital Discharge databaseSNIIRAMFrench National Health Insurance Information SystemVKAsvitamin‐K antagonists

## INTRODUCTION

1

Atrial fibrillation (AF) can lead to significant mortality, morbidity, and cost.^1^, ^2^ Long‐term prophylaxis with anticoagulation therapy is recommended to prevent stroke and systemic embolization in patients with AF presenting an independent risk factor for stroke.^3^ Four non vitamin‐K antagonists oral anticoagulants (NOACs) are currently available: the direct factor Xa inhibitors (rivaroxaban, apixaban, and edoxaban) and the direct factor IIa inhibitor (dabigatran). These four NOACs have demonstrated, in randomized clinical trials, a consistent favorable risk‐benefit profile across a wide range of patients with reductions in stroke or systemic embolism, intracranial hemorrhage, and mortality but increased gastrointestinal bleeds when compared with warfarin.^4^, ^5^, ^6^, ^7^, ^8^

Clinical practice data regarding routine use of the different NOACs largely mirrors the results of clinical trials.^9^, ^10^, ^11^, ^12^, ^13^ In addition, a recent study using the French medico‐administrative databases (SNIIRAM and PMSI), including patients with NVAF who initiated dabigatran or rivaroxaban was previously reported but did not include data on apixaban.^14^ The French Health Authority (HAS) Transparency Commission granted positive appraisal in June 2013 to the reimbursement of apixaban in the indication of stroke prevention and systemic embolism in patients with NVAF, with one or more risk factors, such as prior stroke or transient ischemic attack, age ≥ 75 years, hypertension, diabetes mellitus, and symptomatic heart failure (NYHA ≥ class II). However, while recommending the reimbursement of apixaban in this indication, HAS requested clinical practice data documenting the therapeutic benefit of apixaban under actual conditions of use, compared with the standard oral anticoagulant treatment recommended in France (vitamin‐K antagonists, dabigatran, and rivaroxaban). Indeed, limited clinical practice data are available on the characteristics, clinical management, and outcomes of patients treated with apixaban in France. The availability of warfarin and three NOACs in France allows opportunities for comparative analyses, particularly on the effectiveness and the safety of these drugs when used outside the controlled setting of clinical trials. Nevertheless, as edoxaban was only recently introduced to the market, and not yet available in France, this analysis will only focus on VKAs, dabigatran, rivaroxaban, and apixaban.

The NAXOS study is a nationwide observational retrospective cohort generated from the French National healthcare claims database (SNIIRAM) from which eight distinct sub‐cohorts of anticoagulant‐naive and anticoagulant‐experienced patients diagnosed with NVAF will be identified. The aim of this study is to estimate in a clinical practice setting in France the risk of stroke and systemic thromboembolism, and major bleeding events in NVAF patients treated with various anticoagulants; to describe baseline characteristics; and to compare outcomes between patients initiated by apixaban vs patients initiated by each of the other anticoagulants.

## STUDY OBJECTIVES

2

Primary objectives:
*Effectiveness objective*: To estimate the risk of stroke or systemic thromboembolic events according to the newly initiated anticoagulant treatment (corresponding to the first anticoagulant treatment recorded in the database during the study period), in NVAF patients.
*Safety objective*: To estimate the risk of major bleeding according to the newly initiated anticoagulant treatment, in NVAF patients.

Secondary objectives: In NVAF patients, and according to the OAC treatment, the study intended:To describe demographic and clinical characteristics.To estimate the risk of occurrence of a composite morbidity criterion of stroke, systemic embolism, and major bleeding.To estimate the risk of all‐cause mortality.To describe treatment patterns at anticoagulant initiation and over time.To estimate the healthcare resource utilization.To estimate the off‐label use of apixaban in the French valvular AF population initiating apixaban.In OAC‐naive patients only: To compare baseline characteristics, outcomes (stroke and systemic thromboembolic events, major bleeding, and all‐cause mortality), and healthcare resource utilization rates between patients initiated with apixaban vs patients initiated with each of the other anticoagulant treatments in anticoagulant‐naive patients.

## METHODS

3

### Data source and study population

3.1

The NAXOS study is a French nationwide, observational retrospective cohort of NVAF patients newly initiated with either apixaban, dabigatran, rivaroxaban or VKAs, from which eight distinct sub‐cohorts (Figure 1) of anticoagulant‐naive patients and anticoagulant‐experienced patients (patients treated by anticoagulant before the inclusion date) will be identified.

**Figure 1 clc23231-fig-0001:**
[figure not shown]
Study design. AC, anticoagulant; AF, atrial fibrillation; NVAF, non‐valvular atrial fibrillation

Using the French National Health Insurance System (SNIIRAM) database, patients were identified and included in the study if they initiated a new anticoagulant treatment from 1 January 2014 to 31 December 31 2016. The study will be led by a project team, a coordinating center and a scientific board which is detailed in the Supporting Information Appendix 1.

Patients will be followed from the date of their first OAC prescription until the end of follow‐up, which is defined by the occurrence of a following event, whichever comes first:
*Switch to another anticoagulant treatment*: defined as dispensation of another anticoagulant molecule recorded after initiation of the studied anticoagulant treatment. Date of switch (and end of follow‐up) will be the date of the first dispensation of the other anticoagulant molecule.
*Discontinuation*: a patient who remains more than 30 days after the coverage by the last dispensation of studied anticoagulant treatment without refilling it will be considered as stopping this treatment. If a hospitalization occurs within this period, the length of the hospital stay will be deducted from the number of days without refilling of the treatment. For patients treated with VKAs, International Normalized Ratio testing realized during a hospitalization will be counted as a VKA dispensation. International Normalized Ratio testing will be used as a proxy of a VKA prescription only to extend VKA treatment exposure, but it will not be used as an index date. OACs drug coverages will be derived based on the recommended dosage, and the coverage of VKA treatment exposure will be defined as 35 days (ie, the median coverage time in days of VKA treatments, based on prior assessment on claims database). The median number of coverage days will also be calculated in the VKA patient population after data extraction.
*Last patient's health record*: defined by the last care (ie, consultations, dispensations, medical procedures…) recorded in the database before a period of 6 months without any reimbursed care. This includes situations like emigration and geriatric homes entry.
*Patient's death*.
*End of study period*.

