#### Study population

3.1.2

Patients will be included in the study if they are covered by the French national health insurance general scheme, with at least one reimbursement of anticoagulant treatment initiated with an index anticoagulant treatment (either naïve or experienced patients), aged 18 or older at their anticoagulant initiation, and diagnosed with AF in the 24 months prior the anticoagulant treatment initiation.

Patients will be excluded of the study cohorts if they had different types of anticoagulant treatment at the index date, diagnosed with a valvular condition in the 24 months before their anticoagulant initiation or treated for an indication other than stroke prevention in AF in the 6 weeks before their first anticoagulant reimbursement (including index date).

The study population will be identified in the database through consecutive steps as indicated in Figure 2 and detailed in Supporting Information Appendix 2.

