**Figure 2 clc23231-fig-0002:**
[figure not shown]
Global flow chart of the study population. AC, anticoagulant; AF, atrial fibrillation; VKA, vitamin‐K antagonist

Anticoagulant‐naive patients will be defined as patients with no dispensation of anticoagulant treatment during the 24 months before the index date, and anticoagulant‐experienced patients corresponding to the others. Patients in the experienced group will only be included at their first entry. Therefore, all patients aged ≥18 years and covered by the French national health insurance general scheme, with at least one reimbursement for OAC treatments (VKAs, apixaban, rivaroxaban, or dabigatran) between January 2014 and December 2016, and without use of the same OAC in the 24 months before the index date (ie, date of the first dispensation) will be included. Only the first dispensation meeting this criterion determined the index date, that is, a patient could be included only once in the study.

Then, patients selected were allocated to four distinct sub‐cohorts of OAC‐naive patients (ie, with no dispensation of any OAC during the 24 months before the index date), receiving either VKAs, apixaban, rivaroxaban, or dabigatran during the study period. Anticoagulant‐experienced patients corresponded to the others.

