Secondary outcomes:Risk of occurrence of a composite morbidity criterion: unadjusted incidence rate in each sub‐cohort, composite morbidity criterion being defined by stroke, systemic thromboembolic events, and/or major bleeding, whichever occurs first.Risk of all‐cause mortality: unadjusted incidence rate of all‐cause death in each sub‐cohort.Major characteristics of patients and comorbidities, which are summarized in Table 2.Treatment patterns at anticoagulant initiation: Type of the prescriber initiating the anticoagulant treatment (general practitioners, office‐based cardiologists, hospital‐based physicians, and others), dispensed dosages, number of dispensed packaging at anticoagulant initiation, co‐prescription of dispensed treatments (other anticoagulants, antiplatelet agents, nonsteroidal anti‐inflammatory drugs, serotonin‐specific reuptake inhibitors, strong inhibitors of both CYP3A4 and P‐gp, HIV protease inhibitors, anticonvulsants, strong inducer of hepatic enzymes, and antiarrhythmic drugs) in each sub‐cohort.Treatment patterns over time:Adherence to treatment: Continuous Measure of Medication Acquisition version 7 (CMA 7).^16^
Persistence: number and percentage of persistent and non‐persistent patients over the 6 months and the 12 months after index date, time‐to‐event of persistence, median duration of persistence, number and percentage of non‐persistent patients with other anticoagulant therapy administered after discontinuation, during the gap, the number and percentage of persistent patients who had concomitant dispensings of other anticoagulant treatment over the exposure period of the studied anticoagulant, the number and percentage of non‐persistent patients who switched from studied anticoagulant treatment and re‐exposed after the switch during a 1‐year period, in each sub‐cohort.
Healthcare resources utilization description: use of medical visits, nurse acts, drugs packages delivered, biology acts, medical procedures, hospital stays, and sick leaves will be reported as:The number and percentage of patients with at least one reimbursement of a such healthcare resource use during the follow‐up period.The mean, SD, median, percentiles 10 and 90 of the number of care, only in patients with at least one reimbursement of the healthcare during the follow‐up period.

**Table 2 clc23231-tbl-0002:** Major patients characteristics and comorbidities evaluated for each anticoagulant

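### A switch is defined by molecule although VKAs form one class-level arm, so a change within the VKA class ends follow-up, and one listed persistence outcome becomes empty

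*Protocol article*

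**What the plan says.** Section 3.1 of the protocol article lists the events that end follow-up. The first is headed "Switch to another anticoagulant treatment" and is "defined as dispensation of another anticoagulant molecule recorded after initiation of the studied anticoagulant treatment". On timing it adds: "Date of switch (and end of follow‐up) will be the date of the first dispensation of the other anticoagulant molecule". It gives no exception for a change within a class, no allowance for overlap and no requirement of a second dispensation.

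The arms are set in Section 3.1.2, where entry requires "at least one reimbursement for OAC treatments (VKAs, apixaban, rivaroxaban, or dabigatran". VKAs are thus one treatment and one arm, next to three single molecules. Table 2 records previous anticoagulant exposure by class and by molecule, as two separate levels.

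Among the treatment patterns over time, Section 3.2 lists the number and percentage of "persistent patients who had concomitant dispensings of other anticoagulant treatment over the exposure period of the studied anticoagulant". Another item in that list refers to non-persistent patients who switched.

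Section 3.4.1 takes person-years as the sum of follow-up durations. When there is no competing risk, it treats the end of follow-up as non-informative censoring.

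**The concern.** Entry to an arm and exit from it are stated in different units. A patient enters the VKA arm by class but leaves it by molecule. An apixaban, rivaroxaban or dabigatran patient cannot change molecule without changing arm, whereas a VKA patient can. The rule therefore creates a reason for censoring that exists in one arm only and is tied to a treatment change.

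Follow-up time is the denominator of both primary incidence rates and the time axis of the cumulative incidence curves and regression models. One of the three planned comparisons, apixaban versus VKAs, has the affected arm on one side. If patients who change VKA differ in later risk from those who do not, censoring at the change is informative and the VKA rate is distorted.

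Separately, a rule that ends follow-up at the first dispensing of any other anticoagulant leaves no room for an outcome that counts such dispensings while exposure continues.

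**Working it through.** The article states no switch rate, sample size or event rate for this point, so there is no figure of its own to reproduce. The check is a comparison of the text, followed by an illustration on assumed inputs.

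**1. Unit of entry against unit of exit.**
- Entry (Section 3.1.2): VKAs, apixaban, rivaroxaban, dabigatran. One class and three molecules.
- Exit by switch (Section 3.1): another molecule.
- Exit by discontinuation (same list in Section 3.1): one coverage of 35 days for VKA treatment as a whole, and INR testing in hospital extends VKA exposure. Neither depends on which VKA was dispensed, so this neighbouring rule works at class level.
- Table 2 names class and molecule as distinct levels, so *molecule* cannot simply be assumed to mean arm.

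A move from one VKA to another therefore meets the switch definition, although the patient stays in the arm and may have no gap in coverage. In the other three arms the event is impossible. This needs only that more than one VKA is dispensed in the data, which the plural used throughout implies.

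**2. Switch rule against the persistence outcome.**
- A patient counted in Section 3.2 must be persistent and have another anticoagulant dispensed during exposure to the studied one.
- Under Section 3.1 the first such dispensation is the switch and ends follow-up on that date.
- The wording of Section 3.2 places switchers among the non-persistent.

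The group is therefore empty under the rules as written.

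**3. Illustration of lost person-time (all inputs assumed).** Let L be the yearly hazard of ending follow-up for other reasons, d the added yearly hazard from changes within the VKA class, and the horizon 12 months with exponential times.

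Share kept = [(1 − e^−(L+d))/(L+d)] ÷ [(1 − e^−L)/L]

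| L | d | Share kept | Lost |
|---|---|---|---|
| 0.3 | 0.05 | 0.8437/0.8639 = 0.977 | 2.3% |
| 0.3 | 0.20 | 0.7869/0.8639 = 0.911 | 8.9% |
| 1.0 | 0.05 | 0.6191/0.6321 = 0.979 | 2.1% |
| 1.0 | 0.20 | 0.5823/0.6321 = 0.921 | 7.9% |

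Lost person-time is not the same as bias. If those who change VKA have the same later event rate as those who do not, events and person-years fall together and the rate stands. If their later risk is higher, the VKA rate is too low; if lower, too high. The article gives nothing from which to choose.

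**The case against.** The strongest reply is that *molecule* is loose wording in a condensed article. The rule's heading speaks of another treatment, Section 3.1.2 counts VKAs as one treatment, and the full protocol may define both switch and persistence properly. Section 3.2 lists concomitant dispensings, therapy in the gap and switching as separate categories, which suggests that a fuller rule exists. An arm-level intention is plausible. Still, the operative definition and the sentence that dates the switch both say molecule, and the article states them as the rule. The defect lies in stated text, not in a detail left to another document.

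A second reply is that censoring at any other anticoagulant is a legitimate as-treated choice. That holds for a move to a different arm. It does not explain censoring a patient who remains on the class that defines the arm.

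A reader might infer more than the article supports:

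- **Heparin or another parenteral agent ends follow-up, so the VKA arm loses much of its time to bridging.** The literal word is *anticoagulant*, but the article mentions no parenteral agent and uses *anticoagulant* and *OAC* interchangeably. An oral-only meaning is open, and no usage rates are given, so neither a loss from bridging nor a resulting bias can be established.
- **There are two rules for naive patients.** Section 3.1.2 has "patients with no dispensation of anticoagulant treatment during the 24 months before the index date" and later "with no dispensation of any OAC during the 24 months before the index date". These are better read as one rule in two terms. They show that the terms need aligning, not that two cohorts are planned.
- **A second outcome, co-prescription of other anticoagulants at initiation, is also empty.** Section 3.1.2 excludes patients "if they had different types of anticoagulant treatment at the index date", but the co-prescription window is not defined in the article. If it runs beyond the index day, the count need not be zero.

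**Conclusion.** The point holds in two parts. First, the switch rule as written censors VKA patients who change VKA, and only the VKA arm is exposed to this. Second, the rule contradicts the listed outcome on persistent patients with concomitant dispensings. Both follow from the text without any assumed figure, given that more than one VKA is dispensed and that persistence is not defined elsewhere independently of the end of follow-up.

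The size of the effect on the primary rates and on the apixaban versus VKA comparison is unknown, and so is its direction. The 2% to 9% loss of person-time shows scale under assumed change rates and is not an estimate. The rule should be settled before analysis because it sets follow-up for both primary outcomes, but the article does not show that the results would be materially wrong.

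**What to change.** For the analysis, define a switch as the first dispensation of an oral anticoagulant from a different study arm (VKA class, apixaban, rivaroxaban, dabigatran) or of another NOAC. Changes within the VKA class then do not end follow-up.

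State how an overlapping dispensing is told apart from a switch, so that Sections 3.1 and 3.2 agree. One route is to keep censoring for the event rates at the first dispensation from a different arm and, for the descriptive outcome only, to judge persistence on refills of the index drug alone. If later refills were instead used to decide whether censoring applies, the rule would draw on information from after the date in question, and that should be avoided.

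State whether non-oral anticoagulants count, and use one term, *OAC* or *anticoagulant*, in the switch rule, the index-date exclusion, the naive definition and the persistence outcomes.

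The cost is a small change to wording and code lists, with no new data. Some VKA patients will keep longer follow-up than under the present rule. Reporting how many patients change VKA, and when, would show how much the choice matters.

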
Despite the numerous advantages related to the use of the SNIRAM database in pharmacoepidemiology studies, this database has limitations. First, there is a risk of incomplete data collection due to the research method using identification of patients through ICD‐10 diagnosis in the SNIIRAM database. Therefore, an algorithm needs to be applied to catch AF patients and can induce a diagnosis bias. Second, only major bleeding resulting in hospitalization is collected through PMSI. Less severe bleeding, requiring emergency care but no hospitalization will not be identified in the database. Third, due to the claim‐based retrospective nature of our study, treatment discontinuation of VKA could be biased due to the nature of individual variable dosing of VKA. Nevertheless, algorithms were performed to overcome these issues. In addition, as we used INR testing during hospitalization as a proxy for VKA dispensation, we might have miss patients who presented temporary interruption of their anticoagulant treatment. As the HAS requested clinical practice data documenting the therapeutic benefit of apixaban under actual conditions of use, compared with the standard oral anticoagulant treatment recommended in France (vitamin‐K antagonists, dabigatran, and rivaroxaban), only apixaban off‐label use were collected and therefore, off‐label data on other anticoagulants could not be reported. Fourth, one of the main limitations of this database, as is the case for many administrative databases, is the lack of information for certain clinical or biological risk factors for stroke, thromboembolism or bleeding. Without such information it is not possible to compare the distribution of these risk factors between anticoagulant treatments. Adjusting/matching for large numbers of covariates ascertain from patients' healthcare claims data improved control of confounding, as these variables could collectively be proxies for unobserved factors. Finally, future analyses of this study could also include complementary comparative approaches, such as using IPTW, which is another and probably better method to estimate an average treatment effect in the entire population if the treatment might be offered to every member of the population (ATE).

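### In-hospital INR tests extend exposure in the VKA arm only, so the same stopping history ends about 20-60 days later on VKA than on a NOAC

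*Protocol article*

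**What the plan says.** The rules are in the discontinuation item of section 3.1 of the protocol article, in the text below Figure 1.

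- **All arms, gap.** Treatment counts as stopped for "a patient who remains more than 30 days after the coverage by the last dispensation of studied anticoagulant treatment without refilling it".
- **All arms, hospital stays.** If an admission falls in that period, "the length of the hospital stay will be deducted from the number of days without refilling of the treatment".
- **VKA only.** "International Normalized Ratio testing realized during a hospitalization will be counted as a VKA dispensation". The next sentence gives the purpose: "International Normalized Ratio testing will be used as a proxy of a VKA prescription only to extend VKA treatment exposure". A test cannot set an index date, so the proxy can lengthen exposure but never start or shorten it.
- **Coverage.** "OACs drug coverages will be derived based on the recommended dosage", whereas for VKA "the coverage of VKA treatment exposure will be defined as 35 days".

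Discontinuation, switch and death are among the events that end follow-up. The abstract counts major bleeding over the exposure period, and section 3.4.1 builds person-years from follow-up durations. The limitations in section 4 state that "as we used INR testing during hospitalization as a proxy for VKA dispensation, we might have miss patients who presented temporary interruption" of treatment.

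**The concern.** An INR measured in hospital does not show that the patient kept taking a VKA after discharge. It may be measured on admission for bleeding, before a procedure, or after the drug has been stopped. The rule asks for no later evidence of VKA use. A patient who stopped before or during the stay is still credited with a new dispensation, and nothing comparable exists for apixaban, rivaroxaban or dabigatran.

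The added time follows a hospitalisation, when event rates may differ from those of stable treatment. Suppose a VKA patient is admitted with a bleed and does not restart. A stroke or death some weeks later can still count as on VKA, while the same event in a NOAC patient with the same history falls after censoring. Section 2 plans the apixaban versus VKA comparison for stroke and systemic embolism, major bleeding and death. The propensity scores in section 3.4.1 use baseline characteristics, so they cannot correct an exposure clock that runs differently by arm after baseline.

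**Working it through.** The article states no bias figure on this point, so there is none to reproduce. The check has two parts.

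**1. Days added by the rule.** Inputs from section 3.1: VKA coverage 35 days, gap 30 days, hospital days deducted from the gap, INR test counted as a dispensation. To isolate the INR rule, both arms get 35 days of coverage. The last dispensation is on day 0, there is no refill or switch, and the admission starts on day a and lasts L days. I assume that coverage from a test runs from the test date.

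- Common rule, stay wholly within coverage: stop declared on day 35 + 30 = 65.
- Common rule, stay beginning within the gap: day 65 + L.
- VKA with an INR test on day t, where t lies between a and a + L: day t + 35 + 30.

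| Admission | Common rule | VKA with INR test | Extra days |
|---|---|---|---|
| day 20, 7 days | 65 | 20+65 to 27+65 = 85-92 | 20-27 |
| day 40, 7 days | 65+7 = 72 | 40+65 to 47+65 = 105-112 | 33-40 |
| day 60, 7 days | 65+7 = 72 | 60+65 to 67+65 = 125-132 | 53-60 |

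With stays of 3 to 14 days at these admission days, the extra time stays within about 20-60 days. An admission before day 20 can add less. Without the INR rule the difference is 0 days.

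Section 3.1 does not say whether follow-up ends when coverage ends or after the 30 days. If it ends with coverage, the difference over the same scenarios is 20-74 days, so the asymmetry is there on either reading.

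**2. Illustrative effect on a rate ratio with no true difference.** All inputs here are assumptions: on-drug rate 3 per 100 person-years; on-drug time exponential with mean 365 days, capped at 1,095 days, so the mean is T = 365 × (1 − e^−3) = 346.8 days; 30 off-drug days in every arm; a share p of VKA patients gaining e extra days; and a rate in off-drug time m times the on-drug rate.

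To first order, rate(off) = 3 × (T + m × off) / (T + off), with off = 30 for NOAC and 30 + p × e for VKA. The ratio is NOAC over VKA.

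| m | NOAC rate | VKA rate, p = 0.1, e = 35 (off = 33.5) | Ratio | VKA rate, p = 0.5, e = 50 (off = 55) | Ratio |
|---|---|---|---|---|---|
| 2 | 3 × 406.8/376.8 = 3.24 | 3 × 413.8/380.3 = 3.26 | 0.99 | 3 × 456.8/401.8 = 3.41 | 0.95 |
| 4 | 3 × 466.8/376.8 = 3.72 | 3 × 480.8/380.3 = 3.79 | 0.98 | 3 × 566.8/401.8 = 4.23 | 0.88 |
| 0.5 | 3 × 361.8/376.8 = 2.88 | 3 × 363.55/380.3 = 2.87 | 1.00 | 3 × 374.3/401.8 = 2.79 | 1.03 |

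With m = 1 the ratio is exactly 1. A calculation that counts only first events gives the same ratios to two decimals.

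**The case against.** The best defence is that the rule repairs a real measurement problem. VKA dosing varies between patients, so a single coverage value will be too short for many of them. Dropping INR evidence could then censor truly treated VKA patients too early, again in one arm only. This stands in part: some of the added time is genuine VKA use. But a test in hospital does not measure outpatient dosing, the gap already tolerates refill intervals of 35 + 30 = 65 days, and the hospital-day deduction already covers in-hospital supply in every arm.

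Other limits also stand. Only the first event of each endpoint counts (section 3.4.2), so a bleed that caused the admission is already recorded and the extension adds nothing to that endpoint. Dispensing of another anticoagulant ends follow-up, so switchers gain no time beyond that date. The comparison is a secondary objective restricted to naive patients. Section 4 discloses that interruptions may be missed, though not that the rule touches one arm or what that does to the comparison. A sensitivity analysis without the rule may exist in the full protocol or analysis plan, so its absence from the article is not the point here.

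Three stronger readings are tempting, and the article does not support them:

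- **That VKA event rates are inflated.** This holds only if risk is higher in the added time. Off-drug time may carry less bleeding, which would dilute the VKA rate.
- **That each affected patient gains a full 65 days.** That is the gross credit from a test. The common rule already keeps part of that time, so the net gain is smaller.
- **That VKA coverage is left open until the data are seen.** Section 3.1 sets 35 days. It adds that "The median number of coverage days will also be calculated in the VKA patient population after data extraction", but nothing says that this median replaces the 35 days.

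**Conclusion.** The asymmetry holds on the article's own text. An arm-specific proxy that can only lengthen exposure is added to rules shared by all arms. For a patient who stops around an admission without switching, it adds about 20-60 days on VKA, given admissions on days 20 to 60 after the last dispensation and stays of 3 to 14 days. On-treatment person-time, later first events, deaths and persistence are affected in the apixaban versus VKA comparison. The common gap and the hospital-day deduction also let some off-drug time into every arm; only the INR-based part is specific to VKA.

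The size and direction of any bias cannot be settled from the article. The ratios of 0.88-0.99 (risk 2-4 times higher in the added time) and 1.00-1.03 (risk halved) rest on assumed shares of 10-50% of VKA patients affected and 35-50 extra days, all counted as off-drug. They show what the rule could do and are not estimates for this study. The point is worth correcting but does not undermine the primary objectives, which are estimates by treatment.

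**What to change.** Run the apixaban versus VKA comparison and VKA persistence under one exposure rule for all arms: dispensed coverage, hospital-day deduction, 30-day gap, no INR extension. Report this beside the INR-extended version, preferably as the main analysis, and base the comparative conclusion on the two agreeing. In the limitations, say that the INR proxy applies to the VKA arm only and that its effect may differ in direction between stroke, death and bleeding.

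The cost is some wording and one rerun of the exposure program. The drawback is that some VKA patients who were truly treated are censored earlier under the common rule, which is why both versions should be shown.
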